## Abstract

**Methods and analysis::**

A randomized, double-blind, parallel, placebo-controlled multicenter trial will be conducted over the course of 2 weeks. A total of 180 CVA patients of ages between 4 and 7 years old will be randomly assigned to the experimental group (XHJJ granules, 4.5 g administered 3 times daily) or control group (matched placebo, 4.5 g administered 3 times daily) in a 2:1 ratio based on subject number per group, respectively. The trial will consist of a 7-day medical interventional stage and a 7-day follow-up stage. On day 7 of the follow-up stage, an evaluation of all subjects will be carried out to assess cough symptom score as the primary outcome and several secondary outcomes, including TCM (traditional Chinese medicine) syndrome score, lung function, and dosage of salbutamol aerosol inhaler therapy. Safety assessments will also be evaluated during the trial.

**Discussion::**

The aim of this study was to examine the effectiveness and safety of Xiehuangjiejing (XHJJ) granule using a trial protocol designed to yield high-quality, statistically robust results for use in evaluating CHM as a treatment for CVA in children.

## 1. Introduction

Cough variant asthma (CVA) was first reported by Corrao in 1979^[1]^ as a disorder that is mainly associated with the clinical symptom of chronic cough without wheezing. This presentation differs from that of typical asthma in spite of the fact that CVA and asthma share pathogenic characteristics of persistent chronic airway inflammation and airway hyper-responsiveness. After CVA was first described in 1980 in 6- to 16-year-old children, results of subsequent studies demonstrated CVA was a common cause of chronic cough (without wheezing or dyspnea) in adults as well.^[2,3]^ Meanwhile, results of another study revealed that CVA accounted for 24% to 29% of chronic cough cases in Europe,^[4]^ while results of a multicenter study of 704 adult patients with chronic cough in 9 hospitals in 8 cities within 5 regions of China revealed CVA rates approaching 32.6%.^[5]^ With regard to pediatric CVA, results of an investigation of etiologies of chronic cough in Chinese children indicated that CVA was diagnosed in 41.95% (1900/4529) of cases, among which CVA rates were highest in children of 3 to 6 years of age.^[6]^ Notably, results of another study revealed that 1/3 of children aged 6 to 14 years with CVA who did not receive timely, effective treatment for the condition subsequently developed typical signs and symptoms of asthma.^[7]^

At present, inhaled corticosteroids (ICSs), oral corticosteroids, bronchodilators (β2-agonists), or leukotriene receptor antagonists are recommended treatments for CVA in adults and children,^[8]^ although ICS treatment efficacy is not known.^[9]^ On the one hand, studies^[10]^ have shown that as compared to oral corticosteroids, ICS administered using a nebulizer works faster and is accompanied by fewer systemic side effects and is thus more appropriate for patients, especially young children, with acute CVA. On the other hand, long-term administration of ICS therapy can cause a hoarse voice, pharyngeal discomfort, and candida infection that usually lead to poor clinical compliance^[11]^ that increased risk of disease relapse, results of one empirical study revealed that discontinuation of ICS for 6 months was associated with a cumulative CVA symptom relapse rate approaching 67%.

Chinese herbal medicine (CHM), which is currently widely used for the treatment of CVA in China,^[12,13]^ appears to be a valid treatment option for pediatric CVA cases, with results of a systematic review and meta-analysis^[14]^showing CHM to be effective and associated with fewer adverse effects relative to other CVA treatments. In fact, CHM administered with combination therapy consisting of ICS together with long-acting beta agonists (ICS/LABA) has been shown to be superior to ICS/LABA alone at reducing serum levels of inflammatory factors (e.g., IL-10, IL-6, TNF), reducing eosinophil levels,^[15]^ and inhibiting airway remodeling.^[16]^

Although many clinical studies have demonstrated that CHM treatment of CVA provides curative effects, many of those studies were methodologically limited due to unclear randomization methods, small sample sizes, inadequate follow-up measures, and so on. Consequently, reliable evidence showing the effectiveness of CHM as a treatment for CVA treatment is lacking, prompting this study to evaluate CHM for inclusion in clinical CVA treatment guidelines as an alternative treatment for the disorder.

Based on traditional Chinese medicine theory, a prescription known as Xiehuangjiejing (XHJJ) granule, which consists of ephedra (mahuang), scorpio (quan xie), Sophorae Flavescentis Radix (kusheng), Semen Armeniacae Amarum (xingren), Ginkgo biloba Linn (baiguo), and Radix Glycyrrhizae (gancao), can warm the lungs, dispel wind, relieve coughing, and reduce sputum production. In fact, most Chinese herbal ingredients in the formulation have been shown to exert beneficial health effects when used as asthma treatments. For example, ephedrine, a main active component of ephedra (mahuang), has been experimentally shown to induce anti-inflammatory and anti-allergic effects by inhibiting release of allergy-associated mediators and promoting selective shrinkage of nasal mucosal blood vessels.^[17,18]^ In recent years, explorations of medicinal asthma treatment formulations have intensified and become increasingly focused on ingredients obtained from insect species,^[19,20]^ such as earthworm (dilong), scorpion (quanxie), silkworm (jiangcang), and cicada (chantui). For example, scorpion venom polypeptides BmKbpp and BmKn2 have been shown to exert beneficial health effects, whereby BmKbpp has been reported to inhibit growth of gram-negative bacteria and BmKn2 has been reported to inhibit *Staphylococcus aureus* growth.^[21,22]^

Previous animal experiments and clinical observations have shown XHJJ prescription to be superior to other treatments in relieving cough, eliminating phlegm, improving lung function, and alleviating airway inflammation. In addition, XHJJ treatment of children with CVA was shown to significantly reduce total numbers of inflammatory cells, numbers of cells belonging to various inflammatory cell subpopulations, and levels of cytokines TNF, IL-6, and IL-1 in bronchoalveolar lavage fluid. Meanwhile, XHJJ treatment of asthmatic mice was shown to down-regulate expression of mitogen-activated protein kinases, the serine–threonine protein kinase Akt, vascular endothelial growth factor, and matrix metallopeptidase 9.^[23,24]^

## 2. Methods/design

### 2.1. Patient and public involvement

Patients or the public were not involved in the design, or conduct, or reporting, or dissemination plans of our research.

### 2.2. Study design

#### 2.2..1. Ethics, consent, and permissions.

This protocol was designed based on implementation of a randomized, parallel, placebo-controlled, multicenter trial. Participants, investigators, outcome assessors, statisticians, and others involved in conducting this trial will be blinded. The trial has been approved by the Institutional Ethics Committee of Jilin Provincial Hospital of Chinese Medicine CCZYFFLL2020-067 and is registered in the Chinese Clinical Trial Registry (ChiCTR2000040906). The study will be conducted in accordance with the principles outlined in the Declaration of Helsinki (2013 version). SPIRIT (Standard Protocol Items: Recommendations for Intervention Trials) guidelines^[25]^ (Additional file 1) will be followed while reporting the protocol for the trial, while CONSORT (Consolidated Standards of Reporting Trials) will be followed while reporting the final results. Written informed consent with regard to the purpose, possible risks, and benefits of this trial will be obtained from each participant prior to enrollment in the trial.

#### 2.2..2. Study design and procedure.

This trial will consists of a 7-day medical intervention stage and a 7-day follow-up stage (Figure 1)and will be carried out concurrently in 6 hospitals in China: the Affiliated Hospital of Changchun University of traditional Chinese medicine (TCM), Changchun; the Affiliated Hospital of Beijing University of TCM, Beijing; the Affiliated Hospital of Liaoning University of TCM, Shenyang; the Affiliated Hospital of Shandong University of TCM, Shandong; the Jiangsu Hospital of TCM, Nanjing; and the First Affiliated Hospital of Henan University of TCM, Henan.

**Figure 1. F1:**
[figure not shown]
Flowchart of this study.

Patients will be invited to participate in an initial assessment (first visit), during which they will be selected or rejected for enrollment according to results of screening based on inclusion and exclusion criteria. Next, eligible patients will receive physical examinations to assess TCM syndrome scores, as well as laboratory testing that will include whole blood counts, routine blood and urine testing, liver and kidney function testing, electrocardiography, and chest radiography. Participants will be randomly assigned to the experimental group (receiving XHJJ granule) or the placebo group and will be blinded with regard to group assignments. Patient self-reported cough symptom scores and TCM syndrome scores will be recorded daily in patient diaries during the treatment period.

Patient face-to-face interviews with blinded assessors will be scheduled on the fourth day (second visit) in order to collect relevant clinical data, including lung function assessments and blood tests, as well as data pertaining to quality of life, safety, and drug usage. Beginning on the seventh day (third visit) and throughout the second week (the follow-up stage), participants will continue to self-report cough symptom scores and TCM syndrome scores daily in their diaries and document their utilization of health resources (including any drug use). During the last visit on day 7, quality of life, lung function, adverse events (AEs), and drug usage will be assessed and participants will undergo blood tests. An overview of specific measurements and time points for data collection is presented in (Table 1).

**Table 1 T1:** Measurement items and point of data capture.

Study period	Screening period (d)	Medication (d)		Safety follow-up
	Visit 1 (−7 to 0)	Visit 2 (4 d)	Visit 3 (7 d)	
Sign informed consent	√			
Fill in general information	√			
Medical history and treatment history	√			
Physical examination	√		√	
chest radiographs	√			
Lung function	√		√	
TCM syndrome score	√	√	√	
Vital signs	√	√	√	√
Routine blood test	√		√	√
Routine urine test	√		√	√
ECG, liver, and kidney function	√		√	√
Adverse event		√	√	√
Distribution of experimental drugs	√	√		
Test drug recovery		√	√	
Issue diary card	√			
Recycle patient’ s diary card			√	
Comorbidity and medication records	√	√	√	
Compliance evaluation		√	√	
Safety assessment		√	√	

### 2.3. Participants

Participants will be recruited based on hospital pediatric outpatient departmental records and invitations to join the study as advertised using posters, newspapers, and online ads. Participants will be included only if they meet all of the following inclusion criteria: meet diagnostic criteria for CVA^[7]^ and a diagnosis of wind and cold attacking the lung^[26]^ are within the age range of 4 to 7 years, Cough symptom severity (daytime + nighttime) score ≧ 4, and Subjects and their guardians voluntarily participate in this clinical trial and provided a signed consent form.

### 2.4. TCM syndrome pattern differentiation

The Chinese syndrome pattern differentiation type indicating pattern of wind and cold attacking the lung will be based on guidelines delineated in the Clinical Research of New Investigational Drugs in Traditional Chinese Medicine, and Guidelines for the Prevention and Treatment of pediatric CVA in Traditional Chinese Medicine.^[27]^ The diagnostic standards are as follows:

Primary signs and symptoms is cough and evident at night or in the morning.Secondary signs and symptoms include little or no phlegm; pharyngeal itching; flow cleaning stuff. The hypoglossal veins are pale purple; turbinate light red and slightly swollen.

Participants will be diagnosed with deficiency of wind and cold attacking the lung syndrome if they have the primary signs or symptoms, at least 3 of the secondary signs or symptoms, and examination of the tongue and pulse indicates syndrome of wind and cold. Investigators at each site will administer a symptom assessment survey to every participant. This will ensure standardized scoring across sites. After being screened for inclusion and exclusion criteria, eligible patients will be entered into the trial.

### 2.5. Exclusion criteria

Patients with one or more of the following characteristics will be excluded: chronic cough due to non-CVA causes; previous receipt of treatments with glucocorticoids, leukotriene modulators, long-acting β receptor agonists, and/or theophylline within 2 weeks prior to enrollment; signs of allergic reactions to the test drug or some components of the drug; Combined with other serious diseases of the system; a history of participation in other trials within the 3 months prior to screening for this trial; and affliction with other conditions that lead the investigator to reject the patient as a participant in this clinical trial.

### 2.6. Interventions

#### 2.6..1. Experimental group.

XHJJ (herb granule, 4.5 g per packet) will be obtained from Hefei Huarun Sanjiu Pharmaceutical Co., Ltd. Participants in the experimental group will be instructed to orally consume one packet of XHJJ dissolved in warm water 3 times per day for 7 days, with each dose consumed one-half hour after a meal.

#### 2.6..2. Control group.

A placebo treatment to simulate XHJJ prescription granules will be produced and packaged by the same manufacturer so that the placebo and XHJJ treatments cannot be distinguished from one another based on appearance of granules and packaging, solubility in warm water, taste, smell, dosage, and method of administration.

Only qualified personnel in each site may dispense drugs to participants and they will make sure that the medicine is kept sealed in a cool, dry, and secure locked place. Drug packaged in each site on returned of the unfinished/empty at every visit, relevant counts and return dates will be recorded on case report forms (CRFs).

### 2.7. Concomitant medications

For severe cough symptoms (cough score ≥ 3), patients will be permitted to temporarily use salbutamol aerosol (Ventolin) as long as they accurately record numbers and times of administration of spray doses. Use of other TCMs, glucocorticoids, and beta agonists, etc. will be prohibited in order to prevent introduction of potential biases into results of the trial.

### 2.8. Randomization, concealment, and blinding

All eligible patients will be randomly assigned to either the experimental group or the control group in a 2:1 ratio reflecting number of subjects per group, respectively. The block randomization sequence will be generated using SAS 9.2 software (SAS, Cary, NC) by an independent statistician, who will not be involved in data analysis.

The allocation sequence will remain confidential prior to unblinding to ensure that all patients, investigators, outcome assessors, and statisticians involved in data analyses will not learn the allocation schedule during the trial. If a major medical emergency occurs, for example serious AEs for which knowledge of the allocation schedule might influence clinical treatment, the corresponding subject’ s randomization code may be obtainable by a requestor who submits an emergency letter to an authorized principle investigator representing the study site associated with the AE.

### 2.9. Outcome measures

#### 2.9..1. Primary outcome.

The primary outcome will be based on the cough symptom score.^[28]^ Mean scores of daytime or nighttime cough severity will be calculated as equal to the total score of daytime or nighttime cough severity divided by the total number of investigational days, respectively.

#### 2.9..2. Secondary outcomes.

TCM syndrome score;Lung function;Dosage of salbutamol aerosol.

#### 2.9..3. Other secondary outcomes.

Laboratory examination findings will be derived from chest X-rays and results of serum allergen-specific IgE detection tests and nitric oxide detection tests. Overall health resource utilization data will be recorded, including doctor visits, hospitalizations, and medication usage.

### 2.10. Safety assessments

The following safety assessments will be performed as follows:

Vital signs: blood pressure, respiration, body temperature, heart rate, etc. at baseline, on day 4, and on day 7; Blood and urine samples, liver function, renal function, electrocardiograms, and chest X-rays will be obtained at the end of the run-in period and at day 4 and day 7. Researchers will be alerted to focus on changes in results occurring among the different time points.

AEs: an AE is any adverse medical event that occurs during the trial, regardless of whether it is related to the drug under evaluation. Patients will be required to report all AEs at each visit. AE characteristics, degree of severity, time of occurrence, duration, AE treatment protocols, and follow-up treatments of AEs will be recorded on case report forms. All AEs will be reviewed to assess causal relationships between AEs and investigational drug according to the standards developed by the Uppsala Monitoring Centre of the World Health Organization.

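### Table 1 contradicts the text on diary return, on day-4 tests and chest films, and on safety tests after the last dose

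*Protocol article*

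**What the plan says.** Section 2.2.2 describes "a 7-day medical intervention stage and a 7-day follow-up stage", "carried out concurrently in 6 hospitals in China". Its text and Table 1, together with section 2.10 and the abstract, set the timing of assessments.

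- **Section 2.10.** "Vital signs: blood pressure, respiration, body temperature, heart rate, etc. at baseline, on day 4, and on day 7". For blood, urine, liver and renal tests, "electrocardiograms, and chest X-rays will be obtained at the end of the run-in period and at day 4 and day 7". No later time point is given for any of these. Adverse events are treated differently: "an AE is any adverse medical event that occurs during the trial".
- **Section 2.2.2, text.** Visit 2 on day 4 includes lung function and blood tests. The sentence on week 2 opens "Beginning on the seventh day (third visit". It then requires daily cough and TCM scores in the diary, and a record of drug use, through the whole follow-up week. A last visit on day 7 covers lung function, adverse events, drug usage and blood tests, among other items.
- **Table 1.** Blood, urine, ECG, liver and kidney tests are ticked at Visit 1, Visit 3 (7 d) and Safety follow-up. Vital signs are ticked at all four columns, lung function at Visits 1 and 3, and chest radiographs at Visit 1 only. The diary card is issued at Visit 1 and recovered at Visit 3. The medication-records row is ticked at Visits 1 to 3 and not at follow-up.
- **Abstract.** Cough score, TCM score, lung function and salbutamol dosage are evaluated on day 7 of the follow-up stage.
- **Section 2.9.3.** "Laboratory examination findings will be derived from chest X-rays", among other sources, with no time point. "Overall health resource utilization data will be recorded, including doctor visits, hospitalizations, and medication usage".

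**The concern.** These are conflicts between statements that the article makes, so they cannot be put down to detail left for a fuller document. Six hospitals running at the same time could each follow a different statement.

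The diary matters most. A site that follows Table 1 takes the card back before the week-2 entries exist. Those entries include the cough score, which is the primary outcome measure. How much of the primary analysis this touches depends on which days enter the mean in section 2.9.1, which does not say whether week 2 counts.

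The other two conflicts concern safety data and burden in children aged 4 to 7. A site that followed section 2.10 alone would do no vital signs, laboratory test or ECG after dosing ends. It would also take two more chest films per child than a site that followed Table 1.

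**Working it through.** No formula in the plan needs reproducing. The check sets the schedules side by side and counts time points per child.

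| Item | Section 2.10 | Section 2.2.2 text | Table 1 |
|---|---|---|---|
| Blood tests | end of run-in, day 4, day 7 | day 4, last visit | screening, day 7, follow-up |
| Urine, liver, renal, ECG | end of run-in, day 4, day 7 | after baseline: no day given | screening, day 7, follow-up |
| Vital signs | baseline, day 4, day 7 | no day given | screening, day 4, day 7, follow-up |
| Chest film | end of run-in, day 4, day 7 | at initial assessment | screening |
| Lung function | not covered | day 4, last visit | screening, day 7 |
| Diary | not covered | daily to end of week 2 | issued at Visit 1, recovered on day 7 |

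**Diary.** Planned days: 7 + 7 = 14. Days after the card is recovered: 14 − 7 = 7. Share: 7/14 = 50%. Table 1 shows no re-issue and no later return, and medication records are not ticked at follow-up. Week-2 scores and drug use therefore have no collection point in Table 1.

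**Day 4.** Section 2.10 asks for the full laboratory set, ECG and film. Section 2.2.2 asks for blood tests and lung function. Table 1 ticks none of these at Visit 2.

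**Laboratory/ECG sets.** Section 2.10 has 3 and Table 1 has 3. *Assuming that the end of the run-in is the screening visit*, they share 2 (screening and day 7), and a site doing everything takes 3 + 3 − 2 = 4. The article describes no run-in elsewhere. If the two time points are separate, they share 1 and the union is 3 + 3 − 1 = 5.

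**Vital signs.** Section 2.10 has 3 and Table 1 has 4. With baseline taken as screening, they share 3, and the only difference is the follow-up.

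**Chest films.** Section 2.10 has 3 and Table 1 has 1, a difference of 2 per child.

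**Lung function after screening.** Section 2.2.2 has 2 time points (day 4 and last visit). Table 1 has 1 (day 7).

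**After the last dose.** Dosing ends on day 7. Section 2.10 has no vital signs, laboratory test or ECG later than that. Table 1 ticks all of them at the Safety follow-up. The column shows no day, which may be an extraction loss, but the mismatch holds whatever the day is.

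**The case against.** The best defence is that a sensible site would read the documents together. The text of section 2.2.2 points to Table 1 for time points, section 2.13 provides training and monthly site audits, and a site could simply do every test that any place mentions. This lowers the chance of divergent practice, and it makes a site following section 2.10 alone unlikely. It does not resolve the diary, because a child cannot write on a card already handed in. Nor does it tell a site whether one film or three is intended.

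A second defence is that the last visit on day 7 means follow-up day 7, where the abstract places the evaluation. That is a natural reading, since the sentence follows the one on week 2. But the same section calls the seventh day the third visit, and Table 1 still recovers the diary and does lung function there. The documents do not settle it.

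Several stronger readings are tempting and are not supported:

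- *The diary is the only source of the cough score.* The abstract names an evaluation of that score on follow-up day 7, and section 2.3 requires a score at entry. A single evaluation does not replace seven daily entries, but it is a second source.
- *A screening-only film loses a listed outcome.* Section 2.9.3 sets no time point for chest X-ray findings, so a screening film can satisfy it.
- *The absence of a quality-of-life row in Table 1 is a contradiction.* The table is presented as an overview, and a missing row is ordinary condensation in an article.
- *Adverse events go uncollected after day 7.* They are defined over the whole trial and ticked at the follow-up.

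The follow-up ticks might also be conditional on an abnormal finding. The article does not say so.

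**Conclusion.** The point stands as three internal contradictions. (1) Table 1 recovers the diary on day 7 although entries are required through week 2, so 7 of 14 days have no collection point in that table. (2) Day-4 laboratory tests, ECG and lung function appear in the text and not in Table 1, and chest films number three in section 2.10 against one in Table 1. (3) Section 2.10 ends vital signs, laboratory tests and ECG at day 7, whereas Table 1 continues them at the follow-up.

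The diary tick is wrong as written. The other two need one consistent answer. The diary, film and post-dose findings rest on tick positions that are legible in Table 1. Only the overlap counts rest on an assumption, namely that the end of the run-in (or baseline) is the screening visit. A reader might infer bias between arms or a loss of power. Nothing in the document supports either, since the same schedule applies to both groups and no sample-size figure depends on it. The corrections should be made, and confidence in the conflicts is high.

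**What to change.** 1. In Table 1, move diary return from Visit 3 to the Safety follow-up, date that column at follow-up day 7 (study day 14) as in the abstract, and tick medication records there.
2. In section 2.10, add this follow-up for vital signs, laboratory tests and ECG. Leave the adverse-event period as it is.
3. In section 2.10, limit the chest film to screening, as in Table 1. Section 2.9.3 need not change. If the sponsor wants a post-baseline film, name its day and tick it in Table 1, giving 1 + 1 = 2 films per child.
4. Give one answer on day-4 laboratory tests, ECG and lung function in sections 2.10 and 2.2.2 and Table 1.
5. Ask the sponsor whether the last visit on day 7, with its lung function test, is on treatment day 7 or follow-up day 7, and align the abstract, section 2.2.2 and Table 1 with the answer. Lung function is a secondary outcome, so its timing is the sponsor's to state.

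Cost: ticks and wording. Diary return adds no attendance, because the blood test and ECG that Table 1 ticks at follow-up already need the child to attend. Following Table 1 on day 4 keeps vital signs and the adverse-event report but gives up the mid-treatment laboratory and ECG check. Keeping that check and the day-4 lung function test adds one laboratory/ECG set and one lung function test per child to Table 1.
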